# B1. PURPOSE OF PROTOCOL

| The overall aim of this clinical research proposal is to demonstrate the feasibility of randomized intervention study comparing the effects of consumption of caffeinated coffee, decaffeinated coffee or water on glucose metabolism. If successful, this study will form the basis for a long-term definitive trial of coffee consumption, body fatness, and glucose tolerance.  Specific aims of this study are:   1. To assess the adherence of randomized participants to their assigned treatment. 2. To determine the effect of caffeinated and decaffeinated coffee consumption on body weight, postload glucose concentrations and markers of insulin sensitivity. |
| --- |

#### B2. SIGNIFICANCE AND BACKGROUND FOR THE STUDY

| In the United States, 16 million persons, or almost 9% of adults, had diabetes in 2002 (1). Worldwide, an estimated 171 million persons have diabetes, and an alarming increase to 366 million persons is expected for the year 2030 (2). Type 2 diabetes accounts for 90-95% of all diagnosed cases of diabetes. Diabetes is associated with high rates of morbidity and premature mortality. Obesity increases risk of type 2 diabetes, hypertension, arthritis, cardiovascular diseases, several types of cancer, and premature mortality (3).  While increased physical activity and restriction of energy intake can substantially reduce incidence of type 2 diabetes (4) insight into the role of other lifestyle factors may contribute to additional prevention strategies for type 2 diabetes. Habitual consumption of coffee may have substantial beneficial effects on glucose metabolism according to recent findings of epidemiological studies in the U.S., Europe, and Japan (5). Coffee is among the most widely consumed beverages in the world. Knowledge on both the positive and negative health effects of coffee is important to allow individuals to make informed choices regarding coffee consumption. In addition, data on the health effects of different types of coffee can be used in public health recommendations and may contribute to disease prevention.  Coffee in relation to glucose metabolism and energy balance: potential mechanisms  Coffee is a beverage that contains hundreds of components including substantial amounts of chlorogenic acid, caffeine, magnesium, potassium, niacin (vitamin B3), trigonelline (N-methylnicotinic acid), and lignans (6-9). The table shows a selection of coffee components and suggested mechanisms for effects of these components on glucose metabolism. Most data on effects of coffee components on glucose metabolism are based on animal and *in vitro* studies, and the relevance for the weight gain and the development of type 2 diabetes in humans is currently unclear. However, the results suggest that an effect of coffee consumption on body fatness and glucose metabolism is biologically plausible, and that the effects of coffee cannot be equated with those of caffeine.  *Caffeine:* caffeine intake was associated with an acute reduction of insulin sensitivity in short-term metabolic studies in humans (10,11) This effect reflects decreased glucose storage, probably due to increased epinephrine release (11) Acute effects of caffeine through increased epinephrine levels cannot be extrapolated to long-term effects of coffee consumption, because acute effects of coffee on epinephrine are weaker than expected from its caffeine content (22) and because effects of caffeine on epinephrine levels wane after continued intake (23) Based on animal studies and metabolic studies in humans, beneficial effects of caffeine on glucose metabolism through increased uncoupling protein expression and lipid oxidation have also been suggested (12). Recent findings from observational studies indicate that the inverse association between coffee consumption and risk of type 2 diabetes cannot be explained caffeine. Decaffeinated coffee consumption was also associated with a lower risk of type 2 diabetes and with markers of insulin sensitivity (24,25). These results indicate that components of coffee other than caffeine can affect glucose metabolism, but do not rule out an effect of caffeine on energy balance and glucose metabolism.In rats, caffeine injections reduced energy intake and weight gain, an effect that may have been mediated by increased levels of corticotrophin-releasing factors or sympathetic activation (16). In humans, energy intake was increased during 2 days of caffeine withdrawal (26). In addition, short-term intervention studies have consistently shown that intake of caffeine or caffeinated coffee stimulates thermogenesis and increases energy expenditure (13-15).  Epidemiological studies on coffee consumption and risk of type 2 diabetes  We have recently conducted a systematic review on epidemiological studies on coffee consumption and risk of type 2 diabetes (5). Nine cohort studies on coffee consumption and risk of type 2 diabetes included a total of 193,437 participants and 8394 incident cases of type 2 diabetes. The summary multivariate-adjusted relative risk of type 2 diabetes was 0.65 (95% CI 0.54-0.78) for the highest (≥6 or ≥7 cups per day) and 0.72 (95% CI 0.62-0.83) for the second highest (4-6 cups per day) category of coffee consumption compared with the lowest category of coffee consumption (0 or ≤2 cups per day). In a recent prospective U.S. study, that was not yet included in the meta-analysis, coffee consumption was also inversely associated with risk of type 2 diabetes (27). In cross-sectional studies, coffee consumption was consistently associated with a lower prevalence of impaired glucose tolerance and type 2 diabetes (5). In several, but not all studies, higher habitual coffee consumption was associated with higher insulin sensitivity (5,28). Results from studies that included an oral glucose tolerance test suggested that coffee consumption affected postprandial glucose metabolism, rather than fasting glucose concentrations (5,29). Coffee consumption tends to be associated with lifestyle habits that increase risk of type 2 diabetes (e.g. cigarette smoking, lower physical activity) and more complete adjustment for confounding generally strengthened the observed inverse association between coffee consumption and risk of type 2 diabetes (5). Still, confirmation of the observed inverse association between coffee consumption and risk of type 2 diabetes in randomized trials of coffee consumption with appropriate outcome measures is desirable to completely rule out residual confounding as a potential explanation.    Previous intervention studies  Data from intervention studies on the effect of coffee consumption for longer than 1 day on glucose homeostasis is sparse. In an older study, 14 days of higher decaffeinated coffee consumption was associated with a decrease in plasma glucose concentrations (30). However, this intervention study did not include a control group. In a randomized cross-over study, 4 weeks of very high coffee consumption did not affect fasting glucose concentrations and increased fasting insulin concentration (31). This increase may reflect reduced hepatic extraction of insulin or direct effects of caffeine on insulin secretion,(31) and requires further study. Several studies have tested effects of caffeine intake of glucose levels and observed no effects (5). No randomized intervention studies have examined the effects of coffee consumption for longer than 1 day on postprandial glucose levels. This is of particular importance because coffee consumption was associated with lower postload (during an oral glucose tolerance test), rather than lower fasting glucose concentrations (5).Few studies have examined the effect of caffeine intake on weight loss. Intake of caffeine capsules for 24 weeks did not induce weight loss in obese persons (32). However, in an other study overweight and moderately obese persons who were habitual caffeine consumers lost more weight during a dietary intervention than those that did not consume caffeine (33).  Study significance:  Epidemiological studies have consistently shown an association between higher coffee consumption and a lower risk of type 2 diabetes. Confirmation of these findings in randomized trials of coffee consumption is desirable, and no randomized intervention studies of coffee consumption and glucose tolerance lasting longer then 1 day has been conducted. We propose this pilot study to demonstrate the feasibility of such a trial. If successful, this study will form the basis for a definitive trial of coffee consumption, body fatness, and glucose tolerance. Given the extensive use of coffee and the rapidly increasing health burden of type 2 diabetes and other obesity related disorders, such a trial would have important public health implications.  Preliminary Data: We have not yet conducted a coffee consumption trial, but an Australian trial of caffeinated and decaffeinated coffee protocol similar to that in the current study appeared to be well tolerated by participants with satisfactory compliance (34). |
| --- |

#### B3. DESCRIPTION OF RESEARCH PROTOCOL

##### A. Study Design

| For this pilot trial we will use an 8-week randomized intervention study comparing the effects of caffeinated coffee (n=15), decaffeinated coffee (n=15), and no coffee (n=15) consumption (see figure).  the study medications. The 8-week intervention will be preceded by a 2-week run-in phase with no coffee consumption. At the initial visit, the 4 week visit, and the 8 week visit an oral glucose tolerance test (OGTT) will be conducted and measures of body fatness will be assessed. At the 6-week visit a nonfasting blood sample will be obtained to measure caffeine concentrations. Although we recognize the potential advantages of a cross-over study, the compliance to the interventions is uncertain and a cross-over design is particularly sensitive to decreases in compliance over time. The intervention will be blinded to the investigators. The intervention will be double blind with regard to the coffee type that participants receive (caffeinated and decaffeinated); we will ask the participants about whether they notice the type of coffee they receive.  **Screening** **Initial visit** **4 wk visit 6 wk visit** **8 wk visit**   | Run-in-phase (2 weeks)  (No coffee) | - Caffeinated coffee (n=15) - Decaffeinated coffee (n=15) - No coffee (n=15) | | --- | --- |   **Randomization:**  Randomization will be conducted by a statistician that is not involved in the study using blocking and stratification by sex to avoid differences in the proportion of men and women between the three intervention groups (35).  **Interventions:**  Participants in the intervention groups will consume 5 cups of instant caffeinated or decaffeinated coffee. The instant coffee will be provided in prepackaged plastic cups each containing the same amount of coffee that should be used to prepare one cup of coffee by adding hot water and 5 of these plastic cups are included in 1 bag (supply for 1 day). The 1-cup packages will not provide any clues whether they contain caffeinated or decaffeinated coffee. We will instruct participants on how to prepare the coffee, and ask them to consume a cup with every meal, and at mid-morning and mid-afternoon. Participants will be allowed to adjust the amount of added water according to their preferred coffee strength, but coffee should be consumed without caloric sweeteners. Artificial sweetener will be supplied to participants that prefer sweetened coffee. Participants who are randomized to the control (no coffee) intervention will be instructed to consume 5 cups of water. Before the start of the run-in phase, participants will receive dietary advice from a nutritionist to avoid coffee-related and caffeine-containing foods and drinks other than the coffee that will be provided. They will also be instructed to maintain a stable usual diet (including supplement use and alcohol consumption), and stable physical activity patterns throughout the study. In addition, participants are not allowed to use caffeine-containing medications such as certain flu remedies and analgesics or medications that may interact with caffeine including bronchodilators, quinolone antibiotics, monoamine oxidase inhibitors, anxiolytics, ranitidine, corticosteroids, growth hormone, and antihypertensives. To reduce symptoms related to caffeine withdrawal, we will instruct participants to gradually reduce their coffee consumption at the start of the run-in period and after completion of the trial over three days. We will provide extra coffee to the participants to allow this gradual reduction after completion of the trial.  **Visits**  Visits will be arranged as outpatient visits to the GCRC and none of the visits will not require an overnight stay.  1. Screening visit (1 visit)  The screening visit consists of:   - Signing the informed consent - An interview: medical history, medication use, use of drugs and alcohol, habitual physical activity - A physical examination including measurement of weight and height - An electrocardiogram, a urine HCG pregnancy test (women only), and drawing of fasting blood for blood glucose, liver function tests (AST, ALT, alkaline phosphatase), creatinine, and complete blood count (CBC).   2. Consultation nutritionist and run-in period  Subjects will meet with the nutritionist to receive instructions to avoid coffee-related and caffeine-containing food (other than the coffee provided) during the entire study. They will also be instructed to maintain a stable usual diet, and stable physical activity patterns throughout the study. To document adherence with the diet, subjects will be asked to record the type of foods and the food portions eaten for two weekdays and one weekend day for the week before the post-run-in phase visit and the visits 4 and 8 weeks later. Following this consultation, subjects will enter the 2-week run-in phase, which will serve as a washout period for the effects of previous coffee/caffeine use.  3. Post run-in phase and efficacy assessment visits (three visits)  These visits will occur immediately after the run-in-phase and 4 and 8 weeks after that. During these visits we will:   - Measure weight and waist circumference - Assess body composition using bioelectrical impedance analysis. - Measure systolic and diastolic blood pressure. - Collect fasting blood samples and conduct an oral glucose tolerance test drawing blood at 30 min, 60 min, and 120 min after the oral glucose load. Blood samples will be used to measure glucose, insulin concentrations, and lipid profile (LDL, HDL, and total cholesterol, triglycerides) and will be stored for possible future measurement of intermediary factors (e.g. adipokines). - Supply coffee sachets to the participants and provide instructions on how to prepare the coffee ( post run-in phase visit and week 4 visit only) - Count what is left of the provided coffee sachets to assess compliance (week 4 and week 8 visit only). Subjects will be invited to provide their ideas regarding possibilities to improve compliance. - Collect the 3-day dietary records and diaries in which participants will document deviations from the intervention protocol.   4. Visit with nonfasting blood draw (one visit)  This visits will occur in the afternoon 6 weeks after the run-in-phase. During this visit we will measure weight and systolic and diastolic blood pressure and collect a nonfasting blood sample. This sample will be used to measure s**erum caffeine concentrations to assess compliance.**  **Consistency of the provided coffee**  We will obtain instant coffee that is from the same batch to reduce variation in coffee characteristics. Also, we will store the product under optimal conditions (e.g. closed containers) and we will measure the amount of caffeine in caffeinated and decaffeinated coffee samples obtained at the start (that will be frozen) and at the end of the study.  **Technology employed in the study**  Demographic data and medical history: obtained by using a standardized questionnaire.  Anthropometry: Body weight, height and waist circumference will be measured according to standard protocols. The body mass index (BMI) is calculated as the weight (kg) over height2 (meters squared). Body composition will also be assessed by bioelectrical impedance analysis, using a single frequency bioimpedance analyzer (model 101, RJL Systems, Mt. Clemens, MI), and fat-free mass (FFM) and fat mass (FM) will be calculated (36). This method has previously been validated by comparison with DEXA measured FM (r=0.91) (37).  Dietary data: Using 3-day dietary records (2 weekday and 1 weekend day) we will calculate total energy intake, the number and distribution of meals and snacks, macro-and micronutrient intakes, and consumption of foods and drinks (particularly carbonated beverages and dairy using the Nutritionist Five program (First Data Bank, San Bruno, CA).  Assessment of blood pressure: blood pressure will be measured using multiple repeated measured with automatic Dinamap blood pressure meters using measurements after the participants has been seated for at least 5 minutes.  Oral glucose tolerance test (OGTT): An OGTT will be conducted in the morning starting before 10 am. Subjects will be instructed not to eat or drink after 8 pm not to use coffee after 5 pm on the preceding day. The glucose load will consist of 75 g glucose anhydrate in 300 ml of water ingested over the course of 5 min. An intravenous catheter will be placed in the forearm and blood samples will be collected before the oral glucose load (fasting), after 30 min, 60 min, and 120 min.  Laboratory data: Insulin will be measured using ELISA without cross-reactivity for pro-insulin, glucose will be measured using a photometric method. Fasting triglycerides and lipoprotein profile will be measured in a certified clinical lipid lab using standard methods (38,39). **Serum caffeine concentrations will be measured (using HPLC) in nonfasting blood samples obtained at the 6-week visit and in the coffee samples. B**lood samples will be stored for future determination of other possible intermediary effects of coffee using other funding sources.  Assessment glucose tolerance and insulin resistance: We will use the glucose area under the curve and 2-hr glucose as measures of glucose tolerance. Higher coffee consumption was associated with lower 2-hr glucose concentrations during an oral glucose tolerance test in several cross-sectional studies (5,29). We will calculate the ratio between the 30 min increment in insulin to 30 min increment in glucose concentration as a measure of early insulin secretion (40). We will calculate the homeostasis model assessment of insulin resistance calculated using the following formula: insulin resistance = fasting insulin x glucose / 22.5 (41). In addition, we will calculate the composite insulin sensitivity index (CISI) using the formula {10,000/the square root of [(fasting glucose x fasting insulin) x (mean glucose x mean insulin)]} during the oral glucose tolerance test. This measure has been shown in validation studies to provide a reasonably good measure of insulin resistance (42). |
| --- | --- | --- |

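### The protocol says investigators are blinded, but its procedures mask only the type of coffee, so blinding of coffee versus water is unsupported

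*Protocol*

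**What the plan says.** The protocol, section B3.A (Study Design), makes a general claim: "The intervention will be blinded to the investigators". The sentence after it is narrower: "The intervention will be double blind with regard to the coffee type that participants receive (caffeinated and decaffeinated", the bracket naming the two coffee types. Under Interventions, the only masking device concerns the same distinction: "The 1-cup packages will not provide any clues whether they contain caffeinated or decaffeinated coffee". For the third arm: "Participants who are randomized to the control (no coffee) intervention will be instructed to consume 5 cups of water". No sachet, dummy or other supply is described for that arm.

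The post-run-in, week 4 and week 8 visits share one list of tasks, written in the first person plural. It includes "Measure weight and waist circumference", body composition, blood pressure and the glucose tolerance test. The same list includes "Supply coffee sachets to the participants and provide instructions on how to prepare the coffee" (post-run-in and week 4) and "Count what is left of the provided coffee sachets to assess compliance" (weeks 4 and 8), an invitation to comment on compliance, and collection of dietary records and deviation diaries.

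Serum caffeine is a further compliance measure: "At the 6-week visit a nonfasting blood sample will be obtained to measure caffeine concentrations". The section does not say who sees these values or when. The only role described as independent of the study is the statistician who randomizes.

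**The concern.** A claim that investigators are blinded, with no arm excepted, tells a reader that all three pairwise comparisons were made by people unaware of assignment. The written procedures deliver that for one comparison at most. Handing a participant sachets, explaining how to prepare them, counting what is left or reading a diary of deviations shows whether that participant drinks coffee or water.

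The two comparisons against water carry the question in the study title and aims. Section B1 makes adherence the first specific aim, and section B3.B lists waist circumference among the outcomes to be analysed. Adherence and side effects are elicited in conversation, and waist is the listed outcome that depends most on the person measuring. Section B3.B also says that the pilot's differences and variation will feed the power analysis of the later trial, so an observer effect could be carried into that calculation. An unqualified claim would probably be repeated when the results are reported.

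**Working it through.** The protocol gives no figure on this point, so the check sets the claim against the procedures, all from section B3.A.

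**1. What each procedure reveals to the person doing it**

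| Procedure | Visits | Coffee versus water | Caffeinated versus decaffeinated |
|---|---|---|---|
| Sachet supply and preparation instructions | Post-run-in, week 4 | Revealed | Masked by packaging |
| Count of remaining sachets | Weeks 4, 8 | Revealed | Masked by packaging |
| Diaries of deviations | Collected at the efficacy visits | Likely revealed once on treatment | Masked unless the participant has guessed |
| Week-6 serum caffeine | Week 6 sample | Not by itself (decaffeinated and water would look alike) | Likely revealed, if individual values are seen |

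The supply item speaks of participants in general. That only the coffee arms receive sachets is an inference, but the control drink is water and nothing equivalent is described.

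**2. Count of what is affected**

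- Participants identifiable as controls: 15 of 15 + 15 + 15 = 45, or one third.
- Pairwise contrasts: caffeinated–decaffeinated, caffeinated–water, decaffeinated–water. Two of the three involve water.

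**3. When the exposure arises**

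At the post-run-in visit, sachet supply is listed after the measurements. If that order is followed, baseline is measured before the supply step reveals anything. By weeks 4 and 8, anyone who dispensed earlier already knows who has coffee.

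Let δ be the amount by which a reader aware of assignment shifts the coffee arm relative to the water arm.

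- Shift only at follow-up: estimated difference in change = true difference + δ.
- Same shift at baseline and follow-up: true difference + (δ − δ) = true difference.
- Mean of weeks 4 and 8, an option in section B3.B: true difference + (δ₄ + δ₈)/2.

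A baseline measured before the arm is known therefore does not protect the change score. The protocol gives nothing from which δ could be estimated, so its size, and even its presence, is unknown.

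**4. Which measures are open to δ**

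- Little affected: glucose, insulin and lipids (laboratory assays) and blood pressure (automated device). Weight and impedance are instrument readings.
- More exposed: waist circumference, compliance discussion, diary review and side-effect reports.

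**The case against.** The first-person plural is the ordinary collective voice of a protocol. The text nowhere says that one person both dispenses and measures, and the visits take place in a clinical research center where tasks could be divided. This stands. A reader might infer that the measuring staff cannot be blind, or that the stated blinding does not exist. The protocol does not support that; it shows only that no arrangement is written that would make the claim true.

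The double-blind sentence already limits itself to coffee type, which implies that participants know whether they drink coffee or water. That is right for participants, but it does not qualify the separate sentence about investigators.

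The measurements are already listed before sachet handling, so a change of order may be unnecessary. This stands in part: the list is not declared a sequence, and order within a visit would not re-blind someone who dispensed at an earlier one. Separation of tasks is what matters.

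The effect on the main targets is small. Section B1 names adherence, body weight, postload glucose and insulin sensitivity; waist is not among them. This stands, and it limits the point. Adherence, however, is the first aim and is among the exposed data.

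The caffeine results may never reach investigators before the analysis, and their handling may be settled in documents not shown. This also stands: the risk is conditional. Section B5 gives the principal investigator complete control over all data, and nothing in the protocol delays access to these values.

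**Conclusion.** The claim that investigators are blinded is unsupported for coffee versus water, and so for both contrasts against control. Blinding of caffeinated versus decaffeinated is supported by the packaging, provided that individual caffeine values are not seen early.

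The conclusion rests on two assumptions: that water participants receive no sachets, and that no separation of tasks exists beyond what is written. The exposure is mainly at weeks 4 and 8, and mainly in waist circumference, adherence, diary and side-effect data.

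A reader might go further and conclude that the glucose and insulin results are biased by observers, or that baseline is compromised. The documents support neither: the first are assays, and the baseline measurements are listed before sachets are supplied. No bias size can be given. This is an overstated claim with an inexpensive remedy, and it does not put the design in doubt.

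**What to change.** - Restrict the blinding statement to caffeinated versus decaffeinated coffee. State that coffee versus water is open to participants and to whoever handles supplies.
- Assign sachet supply, preparation instructions, counts and diaries to existing staff who do not take the outcome measurements. Ask participants not to mention their drink to the measuring staff.
- Withhold individual week-6 caffeine results from investigators until the outcome data are locked.

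The cost is some reallocation of staff time at the three efficacy visits, a few lines of text and a less favourable blinding statement. It is not free: the nutritionist, for example, is described only for the consultation before the run-in, so using that person would add visits to the role. Adherence and diary data will still be collected by people who know coffee from water, and the report should say so. If tasks cannot be split, restrict the claim and withhold the caffeine results; the text would then be accurate, but waist would remain exposed.

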### B. Statistical Considerations

| SAS 8.2 (SAS Institute Inc., NC, USA) will be used for statistical analyses. All safety and adverse event data will be summarized separately for each group. The statistical analysis of the data will follow a standard intention to treat analysis. Changes in glucose and insulin concentrations, weight, body mass index (kg/m2), waist circumference, calculated FFM and FM and dietary intake will be evaluated. We will test overall time effects, treatment effects, and time*treatment interactions using ANOVA, and compare the changes in outcome measures between the groups using Student t-tests (if necessary after normalization of the outcome variable, or using the Wilcoxon Rank Sum test). First analyses will be conducted separately for changes between 0 and 4 weeks and for changes between 0 and 8 weeks. If similar results are obtained, the change between 0 weeks and the average of 4 and 8 weeks can be tested to reduce random within person variation. We will also conduct a data analysis stratifying by habitual coffee consumption before the start of the trial (i.e. 1-2 cups, 2-4 cups and >4 cups per day).  A goal of this pilot study is to obtain information on differences in outcome measures and variation to be used in a power analysis for a ‘definite’ trial which will be proposed in a future R01. The available data is insufficient to conduct a power analysis for effects of coffee on the outcome measures at this point, but previous dietary intervention studies of smaller size and shorter duration have been able to detect effects on parameters of glucose metabolism (43). |
| --- |

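### Randomization is stratified by sex but the named arm comparisons carry no sex term, so they are conservative to whatever extent sex predicts the changes

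*Protocol*

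**What the plan says.** Under Randomization in B3, A. Study Design, allocation is made "using blocking and stratification by sex to avoid differences in the proportion of men and women between the three intervention groups". The arms are "caffeinated coffee (n=15), decaffeinated coffee (n=15), and no coffee (n=15) consumption". No block size is given.

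B3, B. Statistical Considerations names the tests:

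- An ANOVA: "We will test overall time effects, treatment effects, and time*treatment interactions using ANOVA".
- Between-arm tests: "compare the changes in outcome measures between the groups using Student t-tests", with normalization of the outcome or a Wilcoxon rank-sum test if needed.
- The scale: "First analyses will be conducted separately for changes between 0 and 4 weeks and for changes between 0 and 8 weeks".
- One stratified analysis: "We will also conduct a data analysis stratifying by habitual coffee consumption before the start of the trial". Habitual consumption was not a randomization factor.

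Sex is not mentioned in the statistical section. No significance level, effect size or SD is given, and on power the protocol says "The available data is insufficient to conduct a power analysis for effects of coffee on the outcome measures at this point".

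**The concern.** Blocking within sex forces the arms to have nearly the same mix of men and women. A difference between men and women therefore hardly contributes to the chance variation of the arm difference. A two-sample t-test does not know this: its error variance still includes the spread between the sexes. If men and women change by different amounts, the reported standard error is larger than the true one, the test rejects less often than its nominal level, and real effects are harder to see.

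With 15 per arm, avoidable loss of precision is unwelcome. There is also a planning consequence. The protocol says that a goal of the pilot is to supply differences and variation for the power calculation of a definitive trial. An unadjusted SD carries any sex variance into that calculation.

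**Working it through.** The protocol states no power, level or SD, so it has no figure to reproduce. The check is how far the named test departs from its nominal level.

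**Inputs from the protocol:** three arms of 15; stratification by sex with blocking; t-tests on changes; no sex term.

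**Assumptions:** two-sided 5% level; normal changes; the same sex split in each arm (8 men of 15, also tried at 5 of 15); share R² of the variance of the changes explained by sex from 0 to 0.20.

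**Formula.** Let σ² be the total variance of the changes. With sex balanced, the true variance of the difference between two arms is (2/15)σ²(1 − R²). The t-test estimates about (2/15)σ². Hence nominal SE / true SE ≈ 1/√(1 − R²).

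Example with σ = 1 and R² = 0.20: nominal SE = √(2/15) = 0.365; true SE = 0.365 × √0.80 = 0.327; ratio 1.118, about 12% too large.

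**Large-sample level.** The test in effect rejects when a standard normal exceeds 1.96/√(1 − R²):

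- R² = 0.05: 1.96 × 1.026 = 2.01, level 4.4%
- R² = 0.10: 1.96 × 1.054 = 2.07, level 3.9%
- R² = 0.20: 1.96 × 1.118 = 2.19, level 2.8%

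**Simulation at the actual size** (two arms of 15, 60,000 trials per setting, simulation error about 0.1 point on the level; power is for a difference of 1 total SD):

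| R² | Male–female gap in change (within-sex SD) | 1/√(1 − R²) | Level, t-test | Level, sex in model | Power, t-test | Power, sex in model |
|---|---|---|---|---|---|---|
| 0 | 0 | 1.000 | 4.8% | 4.8% | 75.2% | 75.0% |
| 0.02 | 0.29 | 1.010 | 4.8% | 5.0% | 75.5% | 76.1% |
| 0.05 | 0.46 | 1.026 | 4.5% | 5.0% | 75.5% | 77.1% |
| 0.10 | 0.67 | 1.054 | 3.8% | 5.0% | 76.0% | 79.5% |
| 0.20 | 1.00 | 1.118 | 2.9% | 5.1% | 77.2% | 84.1% |

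The gap column is √(R²/(0.25(1 − R²))), for an even sex split. With one-third men the t-test level is nearly the same: 4.9%, 4.6%, 3.9% and 3.0% at R² = 0, 0.05, 0.10 and 0.20.

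**Is stratification the cause?** Under simple randomization the same t-test keeps its level: 5.0%, 4.8% and 5.0% at R² = 0, 0.10 and 0.30. The shortfall comes from stratifying and then leaving the stratum out.

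**Planning.** If the later trial adjusts for sex but is sized on the unadjusted SD, its sample size is overstated by the factor 1/(1 − R²): 1/0.95 = 1.05, 1/0.90 = 1.11, 1/0.80 = 1.25.

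**The case against.** The strongest objection concerns scale. Men and women plainly differ in the level of weight, waist, fat mass and fat-free mass, and a reader might infer that R² must be large. But the protocol tests changes, and subtracting the week-0 value removes any stable difference in level. What matters is how much sex explains of a 4- or 8-week change, in people told to keep diet and activity stable. The protocol gives no figure, and it could be close to zero. R² = 0.10 needs a male–female gap in change of 0.67 SD, and R² = 0.20 needs a full SD. This objection stands, and it limits the size of the point. One qualification: the protocol does not say whether the ANOVA with time terms is run on levels. If it is, its treatment main effect is judged against between-person variance, where differences in level by sex remain.

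A reader might also infer that the planned tests do run below 5%. The document does not support that as a fact: it states no level, and at R² = 0 nothing is lost. Up to about R² = 0.02 the loss cannot be told from simulation error.

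This is also a pilot with feasibility and adherence first. The error creates no false positives, and the stated purpose of stratifying, balance of men and women, is met with or without a sex term. All true. But the second specific aim is the effect of coffee on weight, glucose and insulin sensitivity, and the estimates of variation are meant to be used later.

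Finally, covariates are often left to an analysis plan, which may exist. That could cover the ANOVA. It does not cover the between-arm tests: the protocol names a two-sample t-test or rank-sum test, and neither, as named, has room for a stratum.

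**Conclusion.** The mismatch holds, and its consequence is conditional. The named comparisons leave out the one factor on which randomization is stratified. Over an assumed R² of 0 to 0.20 for the changes, standard errors are 0 to about 12% too large, and an assumed two-sided 5% level falls to about 3% at the upper end. The power forgone for a 1 SD difference runs from nothing to about 7 points (77.2% against 84.1%). The effect becomes material only from about R² = 0.10. It is conservative throughout and leaves the estimated arm difference unbiased. Neither R² nor the level is given in the protocol, so the direction is firm and the size is not. The case for changing the plan rests on the small cost of the change rather than on a demonstrated loss.

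**What to change.** In B. Statistical Considerations:

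- Include sex as a fixed factor in the ANOVA.
- Replace the plain t-test on changes with a linear model containing arm and sex.
- Where the rank-sum test is used, stratify it by sex, since it takes no fixed factor.
- Report the sex-adjusted residual SD of the changes for planning the definitive trial.

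The cost is one degree of freedom (28 to 27 in a two-arm comparison of 15 against 15). If sex explains nothing, power for a 1 SD difference goes from 75.2% to 75.0%, which is within simulation error.
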